**Fig. 1 Fig1:**
[figure not shown]
Flow diagram of the study procedure. Participants will be randomized (1:1 allocation ratio) to Op-reha Guide (intervention group) or usual rehabilitation (control group) in the RCT arm. Assessments will be performed at baseline (T0 randomisation), day 1 (T1), day 8 (T2), day 15 (T3), and day 22 (T4) in RCT and observation arms. Notes. RCT = randomised controlled trial, T = time of assessment, PCU = palliative care unit

In our study, specialised rehabilitation is defined as the treatment provided by rehabilitation therapists, occupational therapists, and physiotherapists. The RCT arm will be conducted in PCUs that routinely perform specialised rehabilitation for terminal cancer patients. The participants of the RCT arm will be randomised (1:1) to the intervention group (the Op-reha Guide) and the control group (usual rehabilitation). The observation group will come from PCUs that do not routinely have rehabilitation therapists perform rehabilitation for terminal cancer patients. The control group will be observed in PCUs where only usual rehabilitation for terminal cancer patients occurs. Observation of the intervention group will occur in PCUs that perform rehabilitation based on the Op-reha Guide. Subsequently, we will compare the patients in the intervention group to those in the control group to discover the effects of using the Op-reha Guide versus usual rehabilitation. We will compare the control group with the observation group to quantitatively evaluate the efficacy of usual rehabilitation. The protocol of this study followed the Standard Protocol Items Recommendations for Interventional Trials (SPIRIT) statement [28] and its checklist.

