### Participants and setting

Participants will be recruited from 16 PCUs across Japan. There will be 11 PCUs in the RCT arm and 5 PCUs in the observation arm, and participants will be enrolled according to the inclusion and exclusion criteria. Inclusion criteria are: a) an initial hospitalisation in PCU; b) being 20 years or older at the time when they provide informed consent; c) having a clinical diagnosis of cancer; d) receiving no curative treatment, such as surgery, radiation therapy, or chemotherapy; e) European Cooperative Oncology Group Performance Status (ECOG PS) of 2 or 3; f) having a clinically estimated life expectancy of 3 weeks or more (based on the opinion of investigators and Palliative Prognostic Index of 6 or less); g) starting specialised rehabilitation within 1 week of hospitalisation in PCU (only RCT arm); and h) having the ability to provide written informed consent. Exclusion criteria are: a) having a severe symptom burden (i.e. score of 4 on any of the three Support Team Assessment Schedule items of pain control, other symptom control, and patient anxiety); b) having a respite admission within 1–2 weeks; c) having a weight-bearing limitation due to impending bone fracture; and d) will be undergoing a nerve block anaesthesia or percutaneous vertebroplasty (cement composition).

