#### Statistical analysis

Comparison of the primary endpoint (i.e. mean difference in the change in total mBI from baseline to T4) between the intervention group and control group will be conducted using a two-sided one-way *t*-test with a significance level of 5% according to the intention-to-treat principle. Point estimates and 95% confidence intervals for the mean difference between the two groups will be calculated. This analysis will also be conducted between the control group and observation group. For supplementary analysis that compares the control and observation groups, a multivariate analysis will be conducted with the primary endpoint as the dependent variable, and groups and background information as independent variables. The secondary endpoints of efficacy will be evaluated similarly. For the safety evaluation, the frequency and incidence of adverse events for each group will be calculated. A full statistical analysis plan will be written prior to the data evaluation. All analyses will be performed using SAS version 9.4 (SAS Institute, Cary, NC, USA).

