#### Sample size calculation

To calculate the sample size for the RCT arm, we assumed that the mean difference in the change in total mBI from baseline to T4 would be 10 (standard deviation, 15) between the groups. There was no previous study on the minimal clinically significant difference (MCID) in mBI at the planning stage of this study. Thus, we decided to adopt a 10-point difference compared with usual rehabilitation as the MCID of this study by extrapolating the MCID of the 20-point scale of the BI [46]. Assuming a 15–20% attrition rate, we calculated 90 patients (45 patients in each group) with a two-sided significance level of 5% and a power of 80%. We decided that the sample size of the observation group would also be 45 patients.

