Third, due to ethical concerns, we did not randomise three groups as a whole as this could cause differing participant characteristics between the RCT arm and the observation arm. Since the efficacy of usual rehabilitation on terminal cancer patients has not been examined previously, we need to compare the usual rehabilitation with a group that does not receive any additional specialised rehabilitation as a usual care group. Because we could not ignore the possibility that patients assigned to the observation group might require the specialised rehabilitation, we conducted the observation group in PCUs that not routinely performed specialised rehabilitation.

Furthermore, the patients targeted in this study are in the terminal phase and have a short life expectancy, the risk of withdrawal might be higher than the patients who are not in the terminal phase. It also means that the risk of being unable to adhere to the prescribed intensity, frequency, and time of the protocol intervention may be higher. However, this does reflect the actual status of clinical practice of rehabilitation for terminal cancer patients who are hospitalised in PCUs.

Since this study is the first of its kind, it will contribute to the evidence on efficacy of implementing rehabilitation for terminal cancer patients.

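### For control versus observation, the unadjusted t-test leads and the adjusted model is only supplementary, so the leading estimate is open to confounding and its interval ignores site

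*Protocol article*

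**What the plan says.** The Design section gives the contrast a purpose of its own: "We will compare the control group with the observation group to quantitatively evaluate the efficacy of usual rehabilitation". The Discussion repeats it.

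The Statistical analysis section first sets out a t-test with a mean difference and 95% confidence interval for the randomised groups, then adds: "This analysis will also be conducted between the control group and observation group". Adjustment follows as a second tier: "For supplementary analysis that compares the control and observation groups, a multivariate analysis will be conducted". Its covariates are described only as background information.

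Four other places bear on whether the two groups are comparable:

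- Enrolment and allocation: observation patients are not randomised.
- Participants and setting: "There will be 11 PCUs in the RCT arm and 5 PCUs in the observation arm". The Design section separates these two sets of units by whether rehabilitation therapists routinely treat terminal cancer patients there. The criterion on starting specialised rehabilitation within a week of admission applies to the RCT arm only.
- Data collection: Day 1 is the day rehabilitation starts in the RCT arm, but is tied to the hospitalisation day in the observation group.
- Discussion: three-way randomisation was not done, for ethical reasons, and "this could cause differing participant characteristics between the RCT arm and the observation arm".

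**The concern.** A two-sample t-test on change scores estimates a treatment effect when randomisation has made the groups comparable and patients are independent. Neither condition is secured here. Patients were not allocated between these groups, and each unit supplies patients to only one of them, so a difference between hospitals appears as a difference between groups. ADL is declining in this population, so starting the clock at a different point of the admission could also shift the three-week change with no effect of rehabilitation.

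The randomised comparison sets one form of specialised rehabilitation against another. Control versus observation is the only contrast with patients who receive none. Any statement that specialised rehabilitation works better than usual care would rest on it, and the plan leads with the version that uses none of the baseline information collected to make the groups more comparable.

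**Working it through.** **Inputs from the document.** The mean difference "would be 10 (standard deviation, 15) between the groups"; the test "with a two-sided significance level of 5% and a power of 80" per cent; attrition of 15–20%; 45 patients per group, with the observation group set to the same size; 11 and 5 units.

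**Input not in the document.** The intraclass correlation (ICC) of mBI change within units. The values below are assumptions.

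**Step 1: the plan's own figure.** n per group = 2 × (1.960 + 0.842)² × 15² / 10² = 35.3, so 36. With 20% attrition, 36 / 0.80 = 45. The stated 45 per group reproduces and is not in dispute. For the contrast at issue, I take 36 completers per group.

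**Step 2: the plain t-test.** SE = 15 × √(2/36) = 3.54. With 70 degrees of freedom, the 95% half-width is 1.994 × 3.54 = 7.05 points.

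**Step 3: the same contrast with clustering.** Assume equal recruitment across units within each group. Cluster sizes are then 36/11 = 3.27 for control and 36/5 = 7.2 for observation. The design effect is 1 + (m − 1) × ICC, which gives 1 + 2.27 × ICC and 1 + 6.2 × ICC. The standard error is SE = 15 × √((DE₁ + DE₂)/36). With 16 − 2 = 14 degrees of freedom, the t quantile is 2.145. Type I error comes from simulating the plain t-test with no group difference (40,000 runs per setting).

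| Assumed ICC | DE control | DE observation | SE | Ratio to 3.54 | Half-width, 14 df | Type I error, 36 per group | Type I error, 45 per group |
|---|---|---|---|---|---|---|---|
| 0 | 1.000 | 1.000 | 3.54 | 1.00 | 7.58 | 4.8% | 5.1% |
| 0.02 | 1.045 | 1.124 | 3.68 | 1.04 | 7.90 | 6.1% | 6.2% |
| 0.05 | 1.114 | 1.310 | 3.89 | 1.10 | 8.35 | 7.6% | 8.8% |
| 0.10 | 1.227 | 1.620 | 4.22 | 1.19 | 9.05 | 10.2% | 11.7% |
| 0.20 | 1.455 | 2.240 | 4.81 | 1.36 | 10.31 | 15.5% | 18.1% |

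Part of the widening comes from the degrees of freedom alone: 7.05 becomes 7.58 at ICC 0. A separate run of 20,000 simulations at 36 per group gave 6.1%, 7.4% and 10.3% at ICC 0.02, 0.05 and 0.10, which agrees.

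**Step 4: confounding, illustration only.** Suppose the groups differed by 20 percentage points in the share with ECOG PS 3, and such patients lost 10 mBI points more. The bias would be 0.20 × 10 = 2 points. With SE 3.54 and no clustering, the false-positive rate is 1 − Φ(1.99 − 2/3.54) + Φ(−1.99 − 2/3.54) = 8%. A bias of 3 or 5 points gives 13% or 28%. All these inputs are assumed. A wider interval or more patients would not remove such a bias.

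**The case against.** The strongest reply is that adjustment is planned. The article gives a multivariable model to this contrast and not to the randomised one, so the need was seen, and it never labels the t-test here as the main analysis. That stands in part: both estimates are pre-specified, and it would be wrong to say that the plan offers no adjustment. But calling the adjusted model supplementary makes the t-test the leading result, and for a non-randomised contrast that order is wrong.

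Second, the limitation is disclosed and the contrast is secondary. The Background states a single aim and the Study endpoints section a single hypothesis, both about the guide. The Design section calls the other part an additional observational study, and it has no power calculation of its own. This stands and limits the weight of the point. Disclosure does not change which estimate leads.

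Third, the covariate list, the site term and the degrees of freedom belong in the statistical analysis plan, which the article promises before data evaluation. This also stands: their absence is not the point. The stated hierarchy is, and an analysis plan that followed the article would inherit it.

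A reader might go further and infer that the estimate is confounded, or that its interval is certainly too narrow. The document supports neither. It gives no baseline data and no ICC, and at an ICC of 0.02 or less the inflation is small.

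**Conclusion.** The point holds as a fault in the order of the analyses for one secondary, non-randomised contrast. Its leading estimate is open to confounding; the direction and size cannot be found from the document. Its confidence interval is too narrow if outcomes cluster by site. At 36 per group, type I error is about 6%, 7.5% and 10% for ICCs of 0.02, 0.05 and 0.10. These figures rest on an assumed ICC, SD 15 and equal recruitment across units within each group.

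One might infer that the trial's main result is also compromised. It is not: intervention and control patients are randomised within sites, and nothing here bears on that comparison. Nor would reordering the analyses turn this contrast into a test of efficacy. Every unit belongs to one group only, so no model can separate hospital effects from the effect of rehabilitation.

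**What to change.** Change the wording of the protocol and carry it into the analysis plan, before data evaluation:

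- Make the planned adjusted model the main analysis of control versus observation, and report the t-test as descriptive.
- Fix the baseline covariates in advance from those already collected, for example ECOG PS, PPS, PPI, the STAS items and age. Time from admission to Day 1 is a natural candidate given the different Day 1 definitions, but Table 1 does not list it, so confirm that it can be derived.
- Justify how baseline mBI is handled. In non-randomised groups, adjusting a change score for baseline can itself create or remove a difference. Choose one form as main and show the other as a sensitivity analysis.
- Use a random site effect or cluster-robust standard errors, with small-sample degrees of freedom that reflect 16 sites, only 5 of them in the observation group.
- In the objective and conclusions, replace efficacy with an adjusted, non-randomised difference, and state that hospital and rehabilitation effects cannot be separated.

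No extra patients are needed, and the covariates named as examples need no new assessments. The cost is a wider interval: before any precision gained from covariates, the half-width goes from 7.05 to about 7.9–9.1 points at 36 per group for ICCs of 0.02 to 0.10. The claim that can be made is also more modest.

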#### Sample size calculation

To calculate the sample size for the RCT arm, we assumed that the mean difference in the change in total mBI from baseline to T4 would be 10 (standard deviation, 15) between the groups. There was no previous study on the minimal clinically significant difference (MCID) in mBI at the planning stage of this study. Thus, we decided to adopt a 10-point difference compared with usual rehabilitation as the MCID of this study by extrapolating the MCID of the 20-point scale of the BI [46]. Assuming a 15–20% attrition rate, we calculated 90 patients (45 patients in each group) with a two-sided significance level of 5% and a power of 80%. We decided that the sample size of the observation group would also be 45 patients.

## Discussion

Our review of the existing literature found that there has been no randomised study that evaluates the efficacy of specialised rehabilitation for terminal cancer patients hospitalised in PCUs. In this study, we will adopt a multicentre, randomised controlled trial design. This is the most appropriate study design to evaluate the efficacy of a new approach. We also considered a cluster randomised controlled design, but chose an individually randomised controlled design due to the exclusion features of institutions, and expect demographic characteristics and other possible confounders to be adjusted for and the results to be generalizable [47]. In addition, we will conduct an observational study, allowing us to evaluate the efficacy of the control group (usual rehabilitation) quantitatively compared with the observation group (usual care).

We would like to discuss several issues related to practice, operation, and other aspects of the study. First, the risks of contamination from the intervention group to the control group are inevitable because it is not possible to completely separate the therapists providing interventions based on the Op-reha Guide and usual rehabilitation. This means that the efficacy of the guide versus the therapist may be difficult to evaluate. To reduce the risk of contamination, we have taken some measures with operating procedures; the therapists cannot be in charge of the two groups at the same time; only the therapist in charge of patients allocated to the intervention group will be able to access the guide and only for the duration of their intervention.

Second, it is assumed that the therapists cooperating with this study are biased towards being highly motivated and experienced regarding rehabilitation in palliative care units. This may also reduce a difference in efficacy between the intervention and control group.

Third, due to ethical concerns, we did not randomise three groups as a whole as this could cause differing participant characteristics between the RCT arm and the observation arm. Since the efficacy of usual rehabilitation on terminal cancer patients has not been examined previously, we need to compare the usual rehabilitation with a group that does not receive any additional specialised rehabilitation as a usual care group. Because we could not ignore the possibility that patients assigned to the observation group might require the specialised rehabilitation, we conducted the observation group in PCUs that not routinely performed specialised rehabilitation.

Furthermore, the patients targeted in this study are in the terminal phase and have a short life expectancy, the risk of withdrawal might be higher than the patients who are not in the terminal phase. It also means that the risk of being unable to adhere to the prescribed intensity, frequency, and time of the protocol intervention may be higher. However, this does reflect the actual status of clinical practice of rehabilitation for terminal cancer patients who are hospitalised in PCUs.

Since this study is the first of its kind, it will contribute to the evidence on efficacy of implementing rehabilitation for terminal cancer patients.

### Status of the trial

Enrolment started in July 2019. At the time of manuscript submission (July 2020), a quarter of the patients have participated. Thus, we expect to complete recruitment by December 2021.

## Data Availability

Not applicable. The JORTC Data Centre and JORTC Independent Data Monitoring Committee have access to the final dataset of this trial. There is no contractual agreement with regards to investigators’ access restrictions on the dataset.

## Abbreviations

RCT: Randomised controlled trial
ADL: Activities of daily living
QOL: Quality of life
mBI: Modified Barthel Index
EORTC: European Organisation for Research and Treatment of Cancer
QLQ-C15-PAL: Quality of Life Questionnaire Core 15 Palliative care
ECOG PS: European Cooperative Oncology Group Performance Status
PPS: Palliative Performance Scale
STAS: Support Team Assessment Schedule
PPI: Palliative Prognostic Index
MCID: Minimal Clinically Significant Difference
